# Study POPULATION and Study procedures

## 5.1 Inclusion and exclusion criteria, justification of study population

We estimated to include 40 patients in group A (Clinica Luganese Moncucco) and 35 patients in group B (Regional Hospital of Bellinzona) for a total of 75 patients (see Section 6.1).

Inclusion criteria:

• patients need a NGT positioning;

• adult patients (> 18 years);

• patients male and female;

• patients intubated by oro- or naso-tracheal way;

• post-induction curarized patients;

• fasting patients (from at least 6 hours)

Exclusion criteria:

• patient refusal;

• patients with known bleeding diathesis / ongoing bleeding;

• patients at risk of bleeding (defined as thrombocytes <50 G/l, INR> 2.5, aPTT> 70 sec);

• patients with traumatic brain injury / polytrauma;

• patients with esophagus-tracheal fistulas or malformations of the ENT sphere;

• patients with current or previous radiotherapy of the ENT sphere;

• patients unable to give their informed consent due to language barriers;

• women who are pregnant.

## 5.2 Recruitment, screening and informed consent procedure

In both centers, after the EC approval of the study, all patients fulfilling eligibility criteria (see Section 4.1) will be recruited in daily clinical practice through the Project Leader or principal investigator or their designees.

All patients will receive an information sheet and a study-specific consent form describing the study and providing sufficient information for patient to make an informed decision about his/her participation in the study. The patients should not sign the informed consent on the same day when it is delivered to him/her to ensure adequate time for reflection and discussion with relatives or other trusted persons.

Each patient will be informed that the participation in the study is voluntary and that he/she may withdraw from the study at any time and that withdrawal of consent will not affect her subsequent medical assistance and treatment. The patient must also be informed that his/her medical records may be examined by authorized individuals other than their treating physician.

The patient information sheet and the consent form will be submitted to the EC to be reviewed and approved. The formal consent of a patient, using the approved consent form, must be obtained before the patient undergoes the procedures of the study.

The patient should read and consider the statement before signing and dating the informed consent form, and should be given a copy of the signed document. The consent form must also be signed and dated by the investigator (or his designee) and it will be retained as part of the study records.

##

## 5.3 Withdrawal and discontinuation

Patients will be taken off study if they withdraw their consent to participate. In such case data collected until the date of withdraw will be used

## 5.4 Project Schedule

See Table 1 in appendix.

## 5.5 Study procedures

Peri-procedural evaluations

• Before anaesthesia;

• Patient eligibility (inclusion / exclusion criteria);

• Patient registration and recording of clinical and demographic data (height, weight, BMI);

• Anonymization by alpha / numeric code;

• Vital parameters recording: non-invasive arterial pressure, heart rate, respiratory rate.

- Group A patients (Clinica Luganese Moncucco):

• Clinical parameters recorded: COPD diagnosis, pulmonary embolism heart disease;

• Study parameters recorded: endotracheal etCO2, esophageal etCO2.

- Group B patients (Regional Hospital of Bellinzona):

• Clinical parameters: diagnosis of jatal hernia, intake of proton pump inhibitors (PPI), fasting hours, presence of reflux disease, enteral feeding;

• Study parameters: esophageal pH (25 cm from the dental arch), gastric pH (40 cm from the dental arch).

Study duration: 1 year (there is no follow up), including a recruitment period of 12 months

# STATISTICS AND METHODOLOGY

## 6.1 Determination of sample size

Previous studies allow us to estimate an etCO2 tracheal value of around 40 mmHg (CI 30-50 mmHg). In order to have a significant difference between tracheal and esophageal groups, with a power of 90% and a significance level of 0.01 (one-tailed z test), we calculate a number of 35 patients (57). Anticipating a 10% in the registration failure rate, it appears useful to register at least 40 patients for group A. In the same way we estimate an esophageal pH level value around 7 (CI 5 – 8); in order to have a significant difference between esophageal and gastric pH value, with a power of 90% and a significance level of 0.01 (one-tailed z test), we calculate a number of 30 patients. Anticipating a 10% of drop off rate, it appears useful to register at least 35 patients for each measurement of group B.

## 6.2. Statistical analysis plan

We tabulate the distribution of baseline variables across the study sections, summarizing categorical variables by frequencies and percentage and numerical variables either by mean and standard deviations (±SDs), or by medians and interquartile ranges (IQR). Data distribution was verified using a Kolmogorov- Smirnov test.

We checked adherence to the protocol for each patient during the study. We assess and report total adherence rate to our protocol in order to analyse data on the intention-to-treat (ITT) and on the per-protocol (PP) population. Primary analysis is carried out on the ITT population for each study group, irrespective of potential non-adherence to the study protocol. Secondary analyses included analysis on the PP population, concerning the patients enrolled and treated following all the study procedures. The results of the performed analyses on the two populations are compared. All hypothesis tests are one-sided and considered significant if p-value is ≤ 0.01. Analyses are accomplished with the intention-to-treat if not otherwise specified.

In group A we tested the hypothesis of difference in the proportion of etCO2 level into the tracheal group and into the esophageal group (measurements collected in patients enrolled in group A), with the ITT. We executed a z-test for comparison of the two proportions, refusing the null hypothesis of no difference between the two if the p-value was ≤0.01. This to identify the threshold value of etCO2 above which tracheal location of NGT is determined with high precision. Similarly, in group B we tested the hypothesis of difference in the proportion of pH level into the esophageal and gastric group, with the ITT. We carried out a z-test for comparison of the two proportions, refusing the null hypothesis of no difference between the two if the p-value was ≤ 0.01. This to identify the threshold value of pH below which gastric location of NGT is determined with high precision. Statistical analysis was performed using SPSS version 10.0 (IBM, Chicago, IL, USA) for Mac OS.

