# BACKGROUND and rationale

## 3.1 Background

The laying of a naso-gastric tube (NGT) is an extremely common procedure performed in intensive medicine; although the standard NGT insertion is performed at the patient's bed, this procedure is not free of risk. In this setting, serious complications can occur, especially in the sedated, intubated and curarized patient, which does not present the cough reflex; for example, complications in the placement of NGT in the lungs could be consequent potential pneumothorax, pneumonia *ab ingestis*, development of a bronco-pleural fistula, alveolar hemorrhages, etc. Some studies show an incidence of complications in the NGT pose in around 1% of total insertions, which are associated to a high morbidity, leading to an increase of hospital stay, global mortality and health costs (1-8, 10-11, 13-14, 16, 19, 21-24, 36, 38, 45, 53-56, 63-65, 67-69).

Numerous methodologies have been evaluated to recognize the correct positioning of NGT at the gastric level, including different clinical techniques (such as gastric auscultation, fluid from the NGT), ultrasound techniques, etc (7, 15, 18, 39-40, 43, 62). Actually, the diagnostic gold standard is the thoraco-abdominal anterior-posterior radiography, which is considered the only non-invasive method capable of confirming the correct NGT pose at intra-diaphragmatic level. However, this non-invasive method requires the use of ionizing radiation (4 uSv for radiography) which could be repeated multiple time for the same patient. As NGT may need to be repositioned several times during the same hospital stay, will be increase ionizing radiation patient exposure. Moreover, there could be an increase to ionizing radiation exposure for health workers too.

Furthermore, in sedated and intubated patients, the detection cassette is placed under the back. As some patients is hemodynamic or respiratory unstable, the required mobilization in order to place the detection cassette in situ, appears to be a further risk.

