# Study OBJECTIVES and Design

## 4.1 Primary and secondary endpoints

The primary endpoint is to identify the threshold value in the distribution and in the frequency of etCO2 and pH values. The pH values will be compared with the performed X .

The threshold values for etCO2 and for pH will be determined in two groups: group A, with the aim to find a threshold value of etCO2 above which we can be sure that aspiration probe is in the trachea and group B, with the aim to find a threshold value of pH below which we can be certain that NGT is in the stomach.

Further secondary results are expected:

- for patients in group A it will be necessary to perform a sub-analysis for the threshold value in the group of patients suffering from COPD;

- for patients in group B, a sub-group analysis will be performed for the threshold value for patients taking proton pump inhibitors (PPIs), and / or in the presence of an already diagnosed gastro-esophageal reflux disease.

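### Group A's oesophageal etCO2 label is never confirmed, group B's promised X-ray comparison is not carried through, and the ITT rule keeps readings from misplaced tubes under their intended label

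*Protocol*

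**What the plan says.** Protocol 3.1 states that "the diagnostic gold standard is the thoraco-abdominal anterior-posterior radiography". Section 4.1 says of group B: "The pH values will be compared with the performed X". The last word is cut off and is evidently X-ray. No such sentence exists for etCO2.

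Section 4.3 assigns the labels by procedure:
- **Tracheal etCO2:** read through a suction tube lying inside the endotracheal tube.
- **Oesophageal etCO2:** whatever is read after the NGT has been passed. No depth or position check is given.
- **Oesophageal and gastric pH:** aspirates at 25 cm and 40 cm.

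Section 5.5 lists for group A: "Study parameters recorded: endotracheal etCO2, esophageal etCO2". For group B it lists the two pH values. Neither list, nor Table 1 in the appendix, has an X-ray item.

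Section 6.2 sets the analysis: "Primary analysis is carried out on the ITT population for each study group, irrespective of potential non-adherence to the study protocol". The secondary per-protocol (PP) set is patients handled according to all study procedures, and the two sets of results are to be compared.

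**The concern.** Nothing is assigned in this study, so intention-to-treat (ITT) protects no comparison. Its practical effect, by fair inference, is to keep each reading under the site where the tube was meant to be. The PP set does not repair this, because a misplaced tube from which both readings were taken has followed every procedure.

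The goal makes this matter. Section 4.1 wants an etCO2 value above which one can be sure of the trachea and a pH value below which one can be certain of the stomach. A cut-off that demanding is governed by the most extreme reading on the other side, and an airway reading filed as oesophageal would be that reading. Misplacement is foreseeable: 3.1 says the danger is greatest in sedated, intubated, curarized patients without a cough reflex, which is the enrolled population.

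**Working it through.** **1. Confirmation of each label**

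| Reading | Label rests on | X-ray check stated | Carried into 5.5, Table 1, 6.2 |
|---|---|---|---|
| Tracheal etCO2 | endotracheal tube | not needed | – |
| Oesophageal etCO2 | NGT inserted | none | no |
| pH at 25 and 40 cm | insertion depth | 4.1 | no |

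No rule says what happens to a reading that the film contradicts.

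**2. The plan's own figures (6.1).** The allowance reproduces to within one patient: 35/0.9 = 38.9, so 39 against 40 stated; 30/0.9 = 33.3, so 34 against 35 stated. The base sizes of 35 and 30 cannot be reproduced, because 6.1 gives neither standard deviations (SDs) nor proportions. The plan gives no misplacement rate.

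**3. Chance of at least one misplaced tube.** Formula: 1 − (1 − p)^n. The rates p are assumptions. The protocol's figure of about 1% (3.1) is for complications of insertion, not misplacement.

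| p | n = 40 (group A) | n = 35 (group B) |
|---|---|---|
| 0.5% | 18% | 16% |
| 1% | 33% | 30% |
| 2% | 55% | 51% |

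For example, 1 − 0.99^40 = 0.331.

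**4. Effect of one mislabelled reading on the etCO2 cut-off.** The effect was simulated with 40 pairs and 10,000 runs (1,000 for Youden); medians are shown. Assumptions:
- Tracheal etCO2 is normal with mean 40. The SD is 2.5 (the 35–45 range divided by 4) or 5.1 (the 30–50 interval in 6.1 divided by 2 × 1.96).
- Oesophageal etCO2 has mean 12.5 and SD 6.4 (spreading over 0–25), or mean 5 and SD 5, cut at 0. The protocol gives only a value below 25 mmHg.

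| Rule | 0 mislabelled | 1 mislabelled |
|---|---|---|
| Largest oesophageal value | 16–26 mmHg, sensitivity about 100% | 40 mmHg, about 50% |
| Youden | 22–30 mmHg, at least 99% | unchanged |
| 95th percentile | 12.6 or 22.2 mmHg | 13.7 or 23.6 mmHg |

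The 50% does not depend on the assumed SDs. The cut-off becomes a single draw from the tracheal distribution, and a new tracheal reading exceeds such a draw half the time. With two mislabelled readings the largest-value cut-off is about 41–43 mmHg and sensitivity about 29%.

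**5. pH.** Assumptions: gastric mean 3.8, SD 0.3; oesophageal mean 7.75 (midpoint of 6–9.5), SD 0.9; n = 35. One truly gastric reading filed as oesophageal moves a smallest-oesophageal-value cut-off from 5.9 to 3.8 and sensitivity from about 100% to 49%. The opposite error, an oesophageal reading filed as gastric, leaves that cut-off where it is and costs 1/35 = 2.9 points of apparent sensitivity.

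**6. Would the planned test reveal it?** z = (p1 − p2)/√(2p̄(1 − p̄)/n), with n = 40, p1 = 1 and otherwise complete separation.
- None mislabelled: 1/√(2 × 0.5 × 0.5/40) = 8.94.
- One mislabelled: p2 = 1/40 = 0.025 and p̄ = 0.5125, so 0.975/√(2 × 0.5125 × 0.4875/40) = 8.72.

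The test is overwhelmingly significant either way and gives no warning.

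**The case against.** A reader might infer that all three kinds of reading lack confirmation and that one misplaced tube destroys the threshold. The documents do not support that. The tracheal site is fixed by the endotracheal tube. For pH, 4.1 does promise a comparison with the film, and its cut-off wording cannot be held against the plan. The plan also names no rule for deriving the threshold: 6.2 speaks only of high precision and a z-test, and under a Youden or 95th-percentile rule one error is harmless or nearly so. All of this stands and limits the claim.

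Three further objections stand in part:
- The ITT sentence is about non-adherence and does not mention tube position. Keeping mislabelled readings is an inference, but nothing in the plan provides otherwise.
- A PP comparison is planned. As defined, it does not depend on where the tube was.
- The case report form (CRF) is not shown and might hold an X-ray field. Even so, 6.2 gives that field no role in the analysis.

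The film also has limits as a reference. A correctly placed group A tube ends in the stomach, so the film would not show it as oesophageal. Nor can a final-position film verify the 25 cm and 40 cm readings.

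**Conclusion.** The point holds in a limited form. The oesophageal etCO2 label has no stated confirmation, the X-ray comparison promised for pH is not implemented, and the primary set retains any reading from a misplaced tube.

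Whether that matters in numbers depends on two things the protocol leaves open. The first is the misplacement rate: 18% to 55% chance of at least one in 40 patients at assumed rates of 0.5% to 2%. The second is the threshold rule. Under a largest-value rule, which the words sure (4.1) and certain (4.3) suggest for etCO2, one airway reading roughly halves sensitivity. Under the other two rules examined the damage is nil or about 1 mmHg. The result also rests on the assumed site distributions, although the fall to about 50% does not depend on the SDs chosen.

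**What to change.** - **5.5 and CRF:** record the result of the routine X-ray and the tube depth.
- **4.1:** complete the sentence on the X-ray comparison and state the reference standard for each NGT reading.
- **6.2, primary set:** replace the ITT population with readings whose location the film does not contradict.
 - Group A: classify the NGT reading as airway or not airway (digestive tract), because a well-placed tube lies in the stomach on the film.
 - Group B: exclude or relabel pairs where the film shows the tube outside its expected course. State that the film verifies only the final position, not the 25 cm and 40 cm marks.
- **6.2, sensitivity analysis:** repeat the analysis with the as-intended labels. Drop the ITT and PP terms.

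Add no X-rays for the study and leave the group B measurement where it is; 4.2 says the study does not alter routine care.

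The cost is two data fields and rewording of 4.1, 5.5 and 6.2. A few readings will leave the primary set. Readings without a film must be counted and reported as unverified, and 6.2 should say in advance whether they stay in. How many there will be is unknown, since the protocol refers to a performed X-ray only for pH.

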## 4.3 Study intervention

Group A procedure:

Patients needing the installation of a NGT at the Clinica Luganese Moncucco are consecutively enrolled and selected according to the inclusion and exclusion criteria listed below. The enrolled patients, after receiving adequately protocol study explanation and signed the informed consent, are sedated and intubated according to the clinical indications and the local protocols, independently from the ongoing study.

Anaesthesia is performed by a professional anaesthesiologist and an anaesthetist nurse, using standardized procedures according to local routine protocols. Induction and intubation therefore take place independently of the ongoing clinical study, independent from both indications for intubation, the choice of drugs and intubation material. At the end of the procedure, as usual, the secretions are aspirated with a suction tube of 18 Fr of 6mmdiameter. When the tube is inserted into the endotracheal tube, before proceeding with the aspiration of the secretions, a capnometer is attached to its outer end (picture A), measuring the etCO2 value for 10-15 seconds. At the end of the measurement, we proceed with the aspiration of the secretions as usual.

[figure not shown]
Pic. A

We then proceed with the laying of an NGT according to local protocols. Also in this case, once the NGT has been inserted, the etCO2 is measured at the end of the probe (pic A) for 10-15 seconds and its value is recorded in the CRF. At the end of the measurement, the capnometer can be detached, as a standard procedure, and the NGT can be used as usual.

At the end of the procedure, therefore, for each patient, two values ​​of etCO2 are acquired which will allow to obtain two "populations of values" of the etCO2: the values recorded ​​at the endotracheal level and the one recorded at the esophageal level. Through statistical analysis, we will find the "threshold value" above which the value of etCO2 found is certain for a location in the trachea. The expected mean values of etCO2, according to the literature, are 40 mmHg in the trachea (range 35-45 mmHg) and <25mmHg in the esophagus.

Group B procedure:

The group B enrolment will start at the Regional Hospital of Bellinzona. The enrolled patients are sedated and intubated according to the clinical indications and the local protocols, independently from the ongoing study.

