Anaesthesia is performed by a professional anaesthesiologist and an anaesthetist nurse, using standardized procedures according to local routine protocols. At the end of the procedure, once the NGT is inserted, the pH is measured by aspirating the gastric contents and measuring on specific litmus paper the pH values, both at a distance of 25 cm from the mouth (esophageal site) and at a distance of 40 cm (gastric site).

At the end of the procedure, for each patient two values ​​of pH are acquired which will allow to obtain two pH "value populations": a value at esophageal level and a value at the gastric level. Through statistical analysis (see Section 6), we will try to find the "threshold value" below which the pH is suggestive for a localization in the gastric area.

The expected mean values of pH are 3.8 in the stomach (range 3.2-4.4) and 8.5 in the esophagus (range 6-9.5).

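### Both readings come from the same patient, but the named primary test is a two-proportion z-test whose standard variance ignores the pairing

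*Protocol*

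**What the plan says.** Section 4.3 describes paired measurement. For group A: "At the end of the procedure, therefore, for each patient, two values" of etCO2 are acquired, one endotracheal and one esophageal. For group B: "At the end of the procedure, for each patient two values" of pH are acquired, one esophageal and one gastric. Section 5.5 lists both readings among the study parameters for the patients of each group.

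Sections 6.1 and 6.2 use the vocabulary of separate samples. The sample size is justified as "In order to have a significant difference between tracheal and esophageal groups", with a one-tailed z test. The hypothesis in 6.2 for group A is a difference in "the proportion of etCO2 level into the tracheal group and into the esophageal group (measurements collected in patients enrolled in group A"). The analysis for group A reads "We executed a z-test for comparison of the two proportions" and for group B "We carried out a z-test for comparison of the two proportions". The decision rule is "All hypothesis tests are one-sided and considered significant if p-value is ≤ 0.01". The synopsis names the same test. Section 6.2 itself acknowledges that both sets of etCO2 values are "measurements collected in patients enrolled in group A". Neither the synopsis nor 6.1 or 6.2 mentions a paired test, a within-patient difference or a within-patient correlation.

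**The concern.** A z-test for two proportions, in its standard form, computes the variance of the difference as if the two proportions came from different people. Here each patient contributes to both. If the two readings of a patient tend to rise and fall together, the standard error is too large and power is lost. If they tend to move in opposite directions, it is too small and false positives exceed 1%. In either case the stated 0.01 is not the level of the test. This is the only primary test named for either group, and 6.2 says that it serves to identify the threshold.

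**Working it through.** **Inputs from the protocol.** Two readings per patient (4.3, 5.5). One-sided alpha 0.01, so the critical value is 2.326. Power 90%, with 35 evaluable patients in group A and 30 in group B. Registered: 40 and 35 (6.1). Expected etCO2 40 against <25 mmHg and gastric pH 3.8 (4.3). Tracheal etCO2 interval 30-50 mmHg and esophageal pH about 7 (6.1).

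**Inputs assumed, because the protocol gives none.** The within-patient correlation, the proportions, the SDs and the cut.

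**The plan's own figures.** The 35 and 30 cannot be reproduced, since 6.1 gives neither two proportions nor an SD. Many pairs of proportions give 35, for example 0.70 against 0.28 or 0.90 against 0.52. The allowance for losses is in order: 35/0.9 = 38.9 and 30/0.9 = 33.3, against 40 and 35 planned. Taking 10% off the registered numbers leaves 40 × 0.9 = 36 and 35 × 0.9 = 31.5, so n = 36 and 31 are used for the level.

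**Level of the test.** With equal proportions p at the two sites and correlation ρ between the two binary results:

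- true variance of the difference: 2p(1-p)(1-ρ)/n
- variance used by the unpaired z: 2p(1-p)/n
- large-sample size: 1 - Φ(2.326/√(1-ρ))

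A latent correlation r between continuous readings cut at the median gives ρ = (2/π)·arcsin(r), so r = ±0.5 gives ρ = ±1/3. Then 2.326/√(2/3) = 2.849, size 0.22%; and 2.326/√(4/3) = 2.015, size 2.2%. Exact enumeration of the paired table at p = 0.5 gives:

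| Latent r | Unpaired z, n=36 | Unpaired z, n=31 |
|---|---|---|
| -0.5 | 2.6% | 1.9% |
| 0 | 1.2% | 0.9% |
| +0.5 | 0.3% | 0.2% |

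The departures from 1% at r = 0 are discreteness. McNemar's z stays between 0.8% and 1.0% in all six cases; exact McNemar does not exceed 0.6%.

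**Power, illustrative.** 80% against 50%, n = 35, latent r = 0.5: unpaired z 66%, asymptotic McNemar 76%, exact McNemar 66%.

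**One data example.** Suppose 30/36 and 22/36 readings lie above the cut. The unpaired z is 0.2222/√(2 × 0.7222 × 0.2778/36) = 2.10, p = 0.018, however the patients pair up.

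- Discordant pairs 8:0: McNemar z = 8/√8 = 2.83, p = 0.002; exact 1/256 = 0.004. The decision at 0.01 reverses.
- Discordant pairs 11:3: z = 8/√14 = 2.14, p = 0.016; exact 470/16384 = 0.029. The decision does not change.

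**At the separation the protocol expects.** Take etCO2 40 against 25 mmHg, cut at the midpoint 32.5, n = 35, latent r from -0.5 to +0.5.

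- SD 5.1 (half-width 10 divided by 1.96): proportions 0.93 and 0.07; every test rejects essentially always.
- SD 10: proportions 0.77 and 0.23; unpaired z rejects in 98.9-99.9%, asymptotic McNemar in 96.6-99.96%, exact McNemar in 94.9-99.9%.

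For pH 3.8 against 7, cut 5.5, n = 30, SD 1 or 1.5, the unpaired z and asymptotic McNemar both exceed 99.8%.

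**The case against.** The protocol never says that the samples are independent, and it states openly that both measurements come from group A patients. That is fair: independence is inferred from the name of the test and from the word group. But nothing in the text points to a paired version, and the test named is the standard unpaired one.

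The stronger objection concerns consequence. The size figures assume equal proportions and the power figure assumes 80% against 50%; neither comes from the protocol. On the protocol's expected values the choice of test almost never alters the overall conclusion. The primary endpoint in 4.1 is a threshold, and pairing changes neither the two marginal proportions nor a point estimate of the cut. This stands, and it limits the weight of the point.

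A reader might infer that the planned test inflates false positives. The documents do not support that. Inflation needs a negative within-patient correlation, and they give no correlation and no reason to expect a negative one. In the data example, independence would predict about 11.7:3.7 discordant pairs (36 × 30/36 × 14/36 and 36 × 6/36 × 22/36). The 11:3 split is therefore close to independence and the 8:0 split shows only conservatism; neither shows a false positive.

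A reader might also infer that a paired test would restore the 0.01 level by itself. It would not. Section 6.2 fixes no cut and uses the comparison to find one; if the cut is chosen from the same data, no test of proportions at that cut has its nominal level.

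**Conclusion.** The primary test named in 6.2 and the synopsis does not match the paired design in 4.3 and 5.5. Its one-sided 0.01 level holds, to large-sample accuracy, only at zero within-patient correlation. Between latent correlations of -0.5 and +0.5 the true level runs from about 2.6% to 0.2%. That range rests on assumed correlations, equal proportions and a mid-distribution cut. With positive correlation the cost is power, not validity.

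The error should be corrected, but it does not put the expected overall result in doubt: at 40 against 25 mmHg with an SD of 5 to 10, every test considered rejects in about 95-100% of cases. The COPD and the PPI or reflux sub-analyses in 4.1 will have fewer patients and may separate less, so the choice of test could matter more there. The absence of a cut fixed in advance is a separate matter, and curing the pairing does not cure it.

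**What to change.** In 6.1, 6.2 and the synopsis:

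- State that the two readings are paired within patient, and speak of tracheal and esophageal readings (esophageal and gastric in group B) instead of groups.
- Compare the continuous readings with a paired t-test or the Wilcoxon signed-rank test.
- Compare proportions with McNemar's test at a cut fixed in advance, and say which version. The exact version guarantees the level but gave no power gain over the unpaired z in the 80% against 50% example (66% for both). The 76% belongs to the asymptotic version.
- For any interval reported around the threshold, resample patients, not single readings.

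The cost is rewording and a re-stated sample-size basis. No further patients, measurements or data items are needed.
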